### Sequence generation: type of randomisation {21b}

Stratified block randomisation will be used to allocate participants to intervention or control arms using an excel spreadsheet. Stratification will be based on sex at birth (male/female) and number of previous depressive episodes (0/1/2 +).

### Allocation concealment mechanism {22}

The allocation sequence will be stored in a password-protected randomisation Excel file accessible only to unblinded randomisers. The intervention materials are prepared by randomisers in sealed opaque envelopes labelled only with the Participant Identification Number (PIN) and week number. Sessions are returned en masse at the end of a participant’s assigned intervention using pre-paid envelopes addressed to the randomisers, who are the only team members authorised to open and securely store them. This process ensures full concealment of allocation until after trial completion.

### Implementation {23}

Blinded researchers contact the randomisers by email notifying them of a new enrolment. Randomisers assign the next available PIN and provide the relevant sealed envelopes to researchers for weekly posting. Sealed envelopes are then posted by the blinded researchers to participants according to the weekly schedule.

## Assignment of interventions: blinding

### Who will be blinded {24a}

The randomisation team (CF, JY, EU) will be unblinded. All other team members are blinded.

### How will be blinding be achieved {24b}

Blinded team members will see only sealed envelopes and will be unable to access the randomisation files which are password protected and stored in a separate online domain from the remainder of the trial administration files, whose access is restricted to the randomisation team. Blinded team members will see only sealed envelopes and will be unable to access the randomisation files, which are password protected and stored in a separate online domain from the remainder of the trial administration files, whose access is restricted to the randomisation team.

Participants are requested not to disclose their assigned condition to the researchers. Participants will open and complete their booklets remotely and without interaction with the researchers. Should a researcher become unblinded, for example by a participant disclosing their assigned condition during an assessment or check-up call, this will be recorded by the researcher in a protocol violation document.

### Procedure for unblinding if needed {24c}

Unblinding may be requested by the Chief Investigator or Sponsor. In the unlikely case of a team member becoming aware of a clinical emergency (e.g. serious self-harm, suicide, risk of harm to others, psychiatric hospital admission involving a participant) that could be related to the intervention or study procedures, or where there is uncertainty, the following steps will be taken:Team member reports to the Chief Investigator within 24 hChief Investigator consults with the Sponsor, if needed, within 48 hIf unblinding is required, the participant’s allocation will be disclosed by the randomiser team accessing the randomisation file which holds details of the assigned conditionAll instances of unblinding will be documented and reported to the Sponsor who advises on the need to report to the HRA.

## Data collection and management

### Plans for assessment and collection of outcomes {25a}

All clinical, cognitive, and feasibility outcomes will be assessed using validated instruments with well-established psychometric properties, as detailed in the Outcomes {10} section. With the exception of eligibility screening and the MINI MDD module (administered by a trained assessor via telephone), assessments are self-report questionnaires administered using Qualtrics, with participants completing the surveys online while remaining on a video or telephone call with a researcher.

Recruitment team members administering assessor-led measures (e.g. screening calls, MINI MDD) are trained through role-play and supervised to ensure fidelity and accuracy.

### Plans to promote participant retention and complete follow-up {25b}

Participants will receive reminder emails or text messages for each session and before each interim and main assessment, alongside sustained contact with the research team through regular calls at baseline, week 3, post-treatment (week 6), and the 12-week follow-up. To acknowledge participants’ time investment, reimbursement will be provided in line with their level of involvement: a total of £80, divided into four instalments of £20 following completion of (1) the baseline assessment, (2) the first three weekly assessments, (3) the post-treatment assessment, and (4) the 12-week follow-up assessment. Retention will also be supported by the research team remaining available during online assessments to address any technical or procedural questions without interfering in responses.

Participants will be retained in the study wherever possible, even if they initiate therapy or medication during the trial. Participants may opt to continue with outcome assessments only, as an alternative to complete study withdrawal.

### Data management {26}

This study will generate both quantitative (self-report questionnaires, experimental tasks at baseline, post-treatment, and 12-week follow-up) and qualitative data (semi-structured exit interviews at post-treatment) in both paper and electronic format. Electronic data will be stored on secure King’s College London servers, hosted through King’s cloud services. The main datasets will be prepared in both R and SPSS formats, with approximately 60 cases expected. Paper materials (i.e. booklets) will be stored in locked filing cabinets within secure university premises, accessible only to authorised members of the research team.

#### Data entry and quality assurance

For manually entered data (i.e. paper booklet data), a double-entry procedure will be implemented in SPSS. Two independent files will be cross-checked with an automated comparison program, and any inconsistencies will be investigated and corrected. Where relevant, data entry is automated via Qualtrics survey software. Quality will be monitored throughout by generating descriptive statistics and range checks (e.g. detecting implausible values such as out-of-range questionnaire scores or impossible demographic values such as age = 150).

#### Data standards

Data handling will follow the best-practice standards set out by the UK Data Archive, including systematic documentation of data and metadata. The study will be conducted in accordance with the FAIR principles [39]. Pre-registration of study design and analyses will ensure transparency.

#### Pseudonymisation and security

Each participant will be assigned a unique Participant Identification Number (PIN), used both on electronic records and paper booklets. All paper records will carry only participant identification numbers (PINs) and no personal identifiers. All datasets will be stored using these PINs, while the master list linking PINs to personal identifiers (name, contact details) will be kept separately on a secure drive, password-protected at the individual file level, and accessible only to the Chief Investigator (custodian of the trial data). During the active trial, data will remain pseudonymised; after analysis and UK data archive deposit, the master list will be destroyed (estimated August 2026), rendering the data fully anonymised.

#### Archiving and retention

Paper data will be digitised as soon as possible, and electronic copies will be stored on encrypted King’s College London servers. Source paper data will be archived in accordance with King’s Data Retention Schedules Policy.

In line with King’s Records and Data Retention Schedule, data will be retained for 5 years after project completion. After anonymisation, datasets will be deposited in the UK Data Archive (via the ReShare process) with accompanying metadata: a codebook, variable labels, provenance documentation, and a read-me file. An embargo of 12 months will be applied to allow publication of main trial outputs.

#### Governance and access

From 12 months after study completion the anonymised dataset will be openly accessible via UK Data Archive for those participants who have consented to data sharing.

### Confidentiality {33}

All information provided by participants will be treated in strict confidence, in accordance with the Data Protection Act (2018) and UK GDPR. The limits of confidentiality, including circumstances where disclosures may necessitate action (e.g. where a participant is considered at risk of serious harm to self or others), are explained in the participant information sheet and discussed during the informed consent process. During the trial, all participants will be assigned a unique Participant Identification Number (PIN) that will be used in place of personal identifiers on study materials and datasets. Personal identifiers (e.g. names, contact details) will be stored separately from research data on password-protected, access-restricted King’s College London servers. Only authorised members of the research team will have access to these identifiers, solely for the purposes of study coordination. After data collection, pseudonymised datasets will be stored securely and, following the destruction of the master list linking identifiers to PINs, will be fully anonymised before archiving and sharing. At no stage will individual participants be identifiable in study reports, publications, or presentations.

For qualitative data, transcripts of interviews will be pseudonymised during transcription by assigning PINs to the participants and removing or replacing any identifying information (e.g. names of people, places, or organisations). When direct quotes are used in publications or presentations, they will be carefully selected to avoid inclusion of any content that could potentially identify the participant.

## Statistical methods

### Statistical methods for primary and secondary outcomes {27a}

As this is a feasibility trial, formal hypothesis testing will not be undertaken, and no single primary clinical endpoint has been defined. Instead, analyses will focus on descriptive statistics and estimation.

#### Primary outcomes

Feasibility metricsResponse rate: N, percent, who progressed from initial referral to first direct contact.Recruitment rate: N, percent, consenting.Eligibility rate: N, percent, eligible (meeting inclusion and exclusion criteria after screening).Randomisation rate: n, percent, randomised overall and per month against the target of 60 total, five per month.Retention: N, percent, providing data at post-treatment and 12-week follow-up.Assessment completion: N, percent, completion overall and per week throughout the intervention period.Adherence: mean (SD) number of sessions completed out of six, and percentage completing ≥ 80 % (≥ 5/6).Acceptability metricsCredibility and Expectancy Questionnaire: mean (SD) scores summarised by group at baseline and post-treatment.Exit Questionnaire: mean (SD) Likert-scale ratings on overall experience, manageability, and likelihood of future use at week 12.Qualitative Interviews: with a purposive subsample (*n* = 8, intervention arm) varying in gender, depression severity, age, and ethnicity, analysed thematically to explore acceptability, barriers, facilitators, and delivery preferences.Integrity of blindingSuccess of randomisation and concealment summarised descriptively.Percentage of unblindings reported as protocol violationsAnalysis of participants’ guesses of allocation at 12-week follow-up.SafetyFrequencies, severities, and relatedness of all AEs/SAEs by arm will be presented descriptively and tabulated.Qualitative content analysis of AE reports will identify common categories and potential risk factors.

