**Discussion:**

CURED has the potential to address the pressing need for accessible, evidence-based interventions for depression. This feasibility trial will establish whether CURED is feasible, acceptable, and safe. If successful, a fully powered, definitive efficacy randomised controlled trial will be warranted.

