### Outcomes {16}

#### Primary outcomes

As this study is a feasibility evaluation of the CURED intervention, there is no single primary clinical outcome. Instead, (1) feasibility, (2) acceptability, (3) blinding integrity, and (4) safety will be assessed across several domains. These metrics will inform progression criteria for a future definitive RCT.*Feasibility* will be quantified using response, recruitment, eligibility, and randomisation rates; adherence; retention; and weekly assessment completion rate.*Acceptability* will be assessed using quantitative measures (Credibility and Expectancy Questionnaire; Exit Questionnaire) and qualitative interviews exploring user experience, barriers, and facilitators to engagement.*Blinding integrity* will be evaluated by the success of randomisation, percentage of unblindings, and by examining whether participants and researchers can correctly guess allocation at the final 12-week follow-up (last contact point).*Safety* will be evaluated throughout the trial by monitoring and documenting adverse events (AEs) and serious adverse events (SAEs), with frequency, severity, and relatedness recorded at each assessment point.

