### Sample size {19}

As this is a feasibility trial, formal power analysis was not appropriate. Consistent with recommendations that feasibility studies include approximately 25–35 participants per arm [36–38], we set our target sample size at 30 participants per arm (60 participants in total).

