## Trial status

Recruitment began on 16/07/2025, with the first eligible participant randomised on 18/08/2025. Recruitment is estimated to continue until 01/07/2026. Please see the registration here: ISRCTN51689816, https://www.isrctn.com/ISRCTN51689816, registered on 16/06/2025. Protocol version is 1.2 (25/12/2024), approved by London–Fulham Research Ethics Committee on 13/03/2025 (REC reference: 24/LO/0855).

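### Primary feasibility, adherence, blinding and safety proportions are planned without confidence intervals, so the abstract promises more than the analysis can support; two dates also need aligning

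*Protocol article*

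**What the plan says.** **Primary outcomes.** Section {27a}, Primary outcomes, lists response, recruitment, eligibility, randomisation, retention and assessment completion as a number and a percentage. Adherence is a mean (SD) number of sessions plus the percentage completing at least five of six. Unblindings are a percentage. Adverse and serious adverse events are tabulated by arm. No interval is named for any of these. The only trial-level numerical target is for randomisation: "randomised overall and per month against the target of 60 total, five per month".

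**General approach.** The opening of {27a} rules out formal hypothesis testing and says that analyses will concentrate on description and estimation. Section {5} states that the statistical analysis plan is integrated in {27a–d} and that no standalone plan will be published. 95% confidence intervals are specified under Secondary outcomes, in both {16} and {27a}.

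**Sample size {19}.** The protocol cites "recommendations that feasibility studies include approximately 25–35 participants per arm" and continues: "we set our target sample size at 30 participants per arm (60 participants in total".

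**Promised conclusion.** The Discussion part of the abstract says: "This feasibility trial will establish whether CURED is feasible, acceptable, and safe". Section {16} says: "These metrics will inform progression criteria for a future definitive RCT".

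**Dates.** Recruitment opened on 16/07/2025, "with the first eligible participant randomised on 18/08/2025" (Trial status). "Recruitment is estimated to continue until 01/07/2026". Under Pseudonymisation and security, once analysis and archive deposit are done, "the master list will be destroyed (estimated August 2026").

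**The concern.** The primary outcomes of this trial are mostly proportions, and they are the quantities that will decide how a definitive trial is designed. The plan gives them less statistical care than the secondary outcomes, which do carry intervals. A bare percentage from 30 or 60 people is easily read as settled. A retention figure of 80%, or an empty row for serious events, could be taken to show that the trial is feasible and the intervention safe when the data are compatible with much less favourable values.

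Because {5} places the analysis plan inside these sections, a reader cannot assume that the intervals are specified in a separate published plan.

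The dates matter less. A monthly rate without a start date can be scored in more than one way. A destruction date that precedes the last follow-up is inconsistent with the protocol's own sequence.

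**Working it through.** **1. Precision of the primary proportions**

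Inputs: n = 30 per arm and 60 in total (section {19}). The observed counts below are assumptions for illustration; the protocol gives no expected values.

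Exact (Clopper–Pearson) 95% limits for k of n: lower = Beta quantile at 0.025 with parameters (k, n − k + 1); upper = Beta quantile at 0.975 with parameters (k + 1, n − k). For k = 0 the lower limit is 0 and the upper limit is 1 − 0.025^(1/n).

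| Assumed result | Exact 95% CI | Wilson 95% CI |
|---|---|---|
| 48/60 (80%) | 67.7–89.2% | 68.2–88.2% |
| 54/60 (90%) | 79.5–96.2% | 79.9–95.3% |
| 24/30 (80%) | 61.4–92.3% | 62.7–90.5% |
| 27/30 (90%) | 73.5–97.9% | 74.4–96.5% |
| 0/30 events | 0–11.6% | 0–11.4% |
| 0/60 events | 0–6.0% | 0–6.0% |

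For 0/30: 1 − 0.025^(1/30) = 0.116. At 80%, the exact interval is about 21 percentage points wide with 60 people and 31 points wide with 30. Response, recruitment and eligibility rates are counted before randomisation and will usually have larger denominators, so their intervals would be narrower. The protocol does not state those denominators.

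**2. The randomisation target against the recruitment window**

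The plan's own figure: 60 ÷ 5 per month = 12 months.

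- From opening: 16/07/2025 to 01/07/2026 = 350 days; 350 ÷ 30.44 = 11.50 months; 5 × 11.50 = 57.5. Rate needed for 60: 60 ÷ 11.50 = 5.22 per month.
- From first randomisation: 18/08/2025 to 01/07/2026 = 317 days; 317 ÷ 30.44 = 10.41 months; 5 × 10.41 = 52.1. Rate needed for 60: 60 ÷ 10.41 = 5.76 per month.
- Whole calendar months: July 2025 to June 2026 is 12 months, giving 60; August to June is 11 months, giving 55.

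The 60 is therefore recovered on one reading (calendar months from opening) and missed by 2.5 to 8 people on the others.

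**3. Master list**

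A participant randomised on 01/07/2026 reaches 12 weeks at 01/07/2026 + 84 days = 23/09/2026. This is a minimum, since section {20} has materials posted at the start of the week after randomisation. Working back 84 days:

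- From 1 August 2026: anyone randomised after 09/05/2026 is still in follow-up; 53 days × 5 ÷ 30.44 = 8.7 people.
- From 31 August 2026: anyone randomised after 08/06/2026 is still in follow-up; 23 days × 5 ÷ 30.44 = 3.8 people.

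If recruitment runs to 1 July 2026, follow-up, analysis and deposit cannot all be complete by August 2026.

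**The case against.** **Intervals.** Every percentage comes with its count, so any reader can compute an interval. The article condenses a full protocol (version 1.2) that is not shown, and interval format is a detail that an article may omit. The first point is true but leaves the plan's own reporting unchanged. The second is weakened by {5}, which places the analysis plan in these very sections. The protocol does name intervals where it wants them, and the sentence that names them in {27a} stands under Secondary outcomes and lists summaries of scores, not proportions.

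**The abstract's wording.** To establish *whether* something is feasible and safe poses a question and does not assert an answer. Elsewhere the protocol speaks of evaluating and of generating evidence, and adverse events are to be presented descriptively. Nothing says that zero events would prove safety. This stands in part, and it makes the matter one of wording. Even so, establishing whether promises an answer, and the plan states neither precision nor a criterion from which to give one.

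**The calendar.** A reader might infer that the target of five per month contradicts the recruitment window, and that feasibility therefore cannot be shown. The document does not support this. The end date is only anticipated, 5.22 rounds to five, and the gap from opening is 2.5 people against a Poisson SD of about √57.5 = 7.6. The larger gap depends on the date of the first randomisation, which is an observed start-up lag and not a planning assumption. Even 52 lies within the 50–70 implied by 25–35 per arm. No pass or fail rule is attached to either number. What remains is an undefined start date.

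**The master list.** A reader might infer that the link to late participants will be lost before follow-up. The protocol makes destruction conditional on analysis and deposit, so following its sequence would prevent that. Only the estimated date is wrong.

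**Conclusion.** The point holds as a gap in planned reporting. The primary proportions have no stated measure of uncertainty, in a plan that promises estimation and supplies intervals for secondary outcomes. At 30 per arm the omission is material: an observed 80% is compatible with about 61–92%, and no serious events in one arm is compatible with a true risk of up to 11.6%. These figures assume illustrative counts, complete denominators of 30 or 60, and exact two-sided 95% limits.

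The abstract's claim should be read, and preferably written, as estimation. The reason is the missing precision and the absence of criteria; it has nothing to do with the recruitment calendar.

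The two date points are minor inconsistencies. They rest on the anticipated close of 1 July 2026 and, for the number of people still in follow-up, on accrual of five per month. A reader might also want fixed progression thresholds. The protocol says that this trial is to inform such criteria, and it gives no basis for particular cut-offs, so none is proposed here.

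**What to change.** - In {27a}, Primary outcomes, add that every primary proportion will be reported with an exact (or Wilson) 95% confidence interval, overall and by arm where the quantity is defined after randomisation. State the denominator of each.
- Do the same for the number of participants with at least one adverse event and with at least one serious adverse event.
- In the abstract's Discussion, replace *establish whether* with wording such as *estimate the feasibility and acceptability of CURED and describe its safety*.
- State the date from which the monthly randomisation rate is counted, and align that rate, the total of 60 and the 01/07/2026 close. Reaching 60 needs about 5.2 per month from opening or 5.8 from first randomisation; otherwise move the close.
- Move the estimated master-list destruction date to after the last 12-week contact (about 23 September 2026 or later), analysis and deposit, in line with the sequence already written.

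The cost is a few sentences and a few lines of code. No additional data are needed, and the conclusions become somewhat more cautious. If the last participants have not yet completed follow-up, all of this can be recorded as a documented amendment.

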### Criteria for discontinuing or modifying allocated intervention/comparator {15b}

Participants may discontinue or be discontinued if adverse events (AEs), serious adverse events (SAEs), or mood worsening are identified at any point during the study and deemed related to the study procedures. This is assessed using an adverse events checklist (see Harms {17} for more information).

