### Harms {17}

The intervention paradigm, cognitive bias modification for interpretation (CBM-I), has been evaluated in over 100 trials and has consistently been found to be safe and no riskier than standard care [7]. The primary potential harm is temporary distress during task completion for the intervention group when reading content which could trigger depressive thoughts. Prior feasibility data on the predecessor of CURED, CBM-Errors, indicated that participants’ immediate mood was typically unaffected or slightly improved following sessions [12]. Adverse Events (AEs) information will be proactively collected at the 3-week check-in call using an adapted version of the Adverse Events Checklist, and an exit interview will provide a further opportunity for adverse event data gathering. If a participant experiences persistent mood deterioration, distress impairing daily functioning, or any indication of risk to self or others, participation will be paused, a risk assessment made and, if appropriate, clinical care will be arranged (e.g. referral to the participant’s GP or mental health team). All AEs judged to be serious, according to the standard HRA definition, will be reported to the Sponsor and REC in line with governance requirements. All adverse events will be presented descriptively by frequency, relatedness to the intervention, severity and seriousness to provide comprehensive safety data which will be reported in trial outputs.

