### Secondary outcomes

Secondary outcomes will be assessed as candidate primary outcomes and used in providing effect size estimates for power calculations for future trials.Suitability of the candidate primary outcomes will be defined by:Acceptability (feedback on burden and clarity from exit questionnaires),Variability (sufficient spread in scores without floor/ceiling effects),Sensitivity to change, defined as evidence of within-group and between-group score changes over time in the expected direction (mean change scores with 95% CIs).Descriptive statistics will be aggregated by assigned condition and presented in tables, including means, medians, standard deviations, variances, range, 95% confidence intervals and levels of missingness.

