#### Protocol and statistical analysis plan {5}

A statistical analysis plan (SAP) is integrated within this protocol (see Sections {27a–d}). No separate standalone SAP will be published, as is appropriate for a feasibility trial with primarily descriptive statistical methods. Should amendments be required, these will be documented and reported in academic publications in accordance with CONSORT and SPIRIT guidelines.

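### The safety analysis tabulates only recorded adverse events; a by-arm count of participants whose own PHQ-9, BDI-II or GRC worsened would be a cheap supplement

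*Protocol article*

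**What the plan says.** Outcomes {16} makes safety the fourth primary outcome domain. It is assessed by documenting AEs and SAEs, "with frequency, severity, and relatedness recorded at each assessment point". The Safety entry in Statistical methods {27a} follows that definition: "relatedness of all AEs/SAEs by arm will be presented descriptively and tabulated", with a qualitative content analysis of the AE reports.

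Mood worsening appears elsewhere as grounds for stopping or pausing. Section {15b} allows discontinuation for study-related mood worsening and adds "This is assessed using an adverse events checklist". Harms {17} places proactive checklist collection at the week-3 call and pauses participation for persistent deterioration. Section {15c} schedules researcher calls at week 3 and at each main assessment.

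The symptom scores have a different purpose. Under Secondary outcomes they are candidate primary outcomes for a later trial, described by arm and judged partly on "mean change scores with 95% CIs" in the expected direction. The GRC, which asks whether the participant feels worse, the same or better, is listed among the exploratory measures without a stated analysis.

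On the status of this text, section {5} says: "A statistical analysis plan (SAP) is integrated within this protocol". It points to {27a–d} and says that no standalone plan will be published.

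**The concern.** The Abstract says the trial will establish whether CURED is safe. Harms {17} names the main potential harm as temporary distress from content that could trigger depressive thoughts. PHQ-9 and BDI-II measure depressive symptoms directly, and the GRC asks outright about feeling worse. Table 2 gives all three a single schedule, with no distinction by arm.

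None of these data reach the safety analysis as written. An AE entry depends on the participant reporting a problem or a researcher recognising one, and the article does not say that a worsened score leads to an entry. An arm-level mean does not show how many individuals got worse, and the listed range is not said to be a range of individual change from baseline. What is at stake is the completeness of the safety report, not the correctness of the AE table.

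**Working it through.** **1. Design figure.** Sample size {19} gives 30 per arm: 2 × 30 = 60, as stated. No hypothesis test is planned, so there is no power figure to reproduce.

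**2. What each planned summary can show about an individual who worsened.**

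- AE/SAE table by arm: shows the person only if an AE was recorded.
- Content analysis of AE reports: the same limit.
- Means, medians, SDs and range of scores by arm: no count of worsened participants.
- Mean change with 95% CI by arm: no count.
- GRC at week 6: no analysis stated.

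**3. How many could worsen behind an improving mean.** The protocol gives no SD of change, so every input here is assumed. With normally distributed change (negative = improvement), P(change ≥ t) = 1 − Φ((t − mean)/SD), and the expected count is 30 times that.

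| Mean / SD | t = 5: % (of 30) | t = 3: % (of 30) | Ratio |
|---|---|---|---|
| −3 / 5 | 5.5 (1.64) | 11.5 (3.45) | 2.10 |
| −3 / 6 | 9.1 (2.74) | 15.9 (4.76) | 1.74 |
| −4 / 5 | 3.6 (1.08) | 8.1 (2.42) | 2.25 |
| −4 / 6 | 6.7 (2.00) | 12.2 (3.65) | 1.82 |
| −5 / 5 | 2.3 (0.68) | 5.5 (1.64) | 2.41 |
| −5 / 6 | 4.8 (1.43) | 9.1 (2.74) | 1.91 |

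Example, first row: (5 + 3)/5 = 1.6; 1 − Φ(1.6) = 0.055; × 30 = 1.64.

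So 2.3% to 9.1% of an arm (0.7 to 2.7 participants) worsen by 5 or more points although the mean improves. A margin of 3 instead of 5 multiplies the count by 1.7 to 2.4, so the margin has to be written down before results are seen. For BDI-II, a margin of 10 with mean −6 to −10 and SD 10 to 12 doubles every input, so it gives the same 2.3% to 9.1%.

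**4. Chance of seeing a case.** P(at least one of 30) = 1 − (1 − p)^30: 78.5% for p = 5%, 95.8% for p = 10%, 99.9% for p = 20%.

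**5. Precision.** Clopper-Pearson 95% intervals: 0/30 gives 0 to 11.6%; 1/30 gives 0.1 to 17.2%; 3/30 gives 2.1 to 26.5%. With an assumed 24 scored per arm, 3/24 gives 2.7 to 32.4%. For 3/30 against 1/30 the difference is 6.7 points, Newcombe 95% CI −8.2 to 22.5. The counts can describe an arm but cannot separate the arms.

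**The case against.** The strongest reply is that nothing here is wrong. Safety is defined through AEs and analysed through AEs, by arm. That stands: this is an omission of a useful supplement, not a contradiction.

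Second, individual worsening already has a route in. Sections {15b}, {15c} and {17} cover mood worsening at any point, a mood check at week 3 and a pause for persistent deterioration, and {25a} has participants complete questionnaires while on a call with a researcher. The adapted checklist and the full protocol are not shown, and may tie a worsened score to an AE entry. This also stands. A reader might infer that deterioration is ignored, and the document does not support that. The gap is only that the stated analysis does not ensure such participants are counted.

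Third, an SD of change can be recovered from the mean change, its interval and n, and the listed summaries need not be exhaustive. This is true, but it yields only a model-based approximation like the one in the working, while the actual count would be directly available.

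Two stronger readings are tempting and should not be drawn:

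- **AE collection is one-sided.** Harms {17} says "an exit interview will provide a further opportunity for adverse event data gathering", Data management {26} mentions "semi-structured exit interviews at post-treatment", and {27a} restricts its eight qualitative interviews to the "intervention arm) varying in gender, depression severity, age, and ethnicity". A reader might infer that this AE source exists in one arm only. But {17} places no arm restriction on its exit interview, and no section says that it is the same interview as the acceptability interviews.
- **The cut-off would be chosen with knowledge of allocation.** The Chief Investigator and project coordinator are in the unblinded randomisation team, but nothing says they would set a margin or run the analysis. The case for fixing the margin early rests only on how strongly the count depends on it.

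**Conclusion.** The point holds as a low-priority improvement. Safety is a primary outcome analysed only through recorded AEs and SAEs. Symptom scores are summarised only at arm level and the GRC has no stated analysis, so a participant who worsened without an AE entry can be absent from the safety report. Because section {5} presents {27a–d} as the analysis plan, deferral to another plan is a weak answer, although the unseen full protocol could say more.

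The likely size is about one to three participants of 30 per arm. That figure depends on assumed means, SDs, margin and normality, none of which the document gives. No calculation supports the BDI-II item 9 count. It is suggested because {14a} already uses that item to assess suicidal thoughts. The counts would not by themselves establish safety, and no stated progression decision turns on them.

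**What to change.** Add one paragraph to {27a} Safety. Report the following descriptively by arm, with exact 95% confidence intervals and the number not assessed at each time point:

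- (a) n/N rating themselves worse on the week-6 GRC.
- (b) n/N worse than the T0 score at weeks 6 and 12, on PHQ-9 and on BDI-II, by a numerical margin that the trial team writes down before any by-arm outcome table exists. Increases of 5 points on PHQ-9 (range 0 to 27) and 10 on BDI-II (range 0 to 63) are working assumptions only.
- (c) n/N with any increase from T0 in BDI-II item 9 at weeks 6 and 12.

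For (b) and (c), N is the participants with both scores. Use the T0 BDI-II and not the screening BDI-II: participants were selected on a screening score of 15 or more, and regression to the mean from a selected score would hide worsening. State that the counts supplement the AE table, are read against the control arm and are not tested.

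The cost is one paragraph and a few table rows, with no new data, visits or staff. Recruitment is estimated to run to 1 July 2026 and no interim analysis is planned, so the margin can still be set ahead of results. The downside is that intervals are wide and some worsening is natural fluctuation.
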